## Abstract

**Background:**

Implementation scientists and practitioners, alike, recognize the importance of sustaining practice change, however post-implementation studies of interventions are rare. This is a protocol for the Sustainment, Sustainability and Spread Study (SSaSSy). The purpose of this study is to contribute to knowledge on the sustainment (sustained use), sustainability (sustained benefits), and spread of evidence-based practice innovations in health care. Specifically, this is a *post-implementation* study of an evidence-informed, Care Aide-led, facilitation-based quality-improvement intervention called SCOPE (*Safer Care for Older Persons (in long-term care) Environments*). SCOPE has been implemented in nursing homes in the Canadian Provinces of Manitoba (MB), Alberta (AB) and British Columbia (BC). Our study has three aims: (i) to determine the role that adaptation/contextualization plays in sustainment, sustainability and spread of the SCOPE intervention; (ii) to study the relative effects on sustainment, sustainability and intra-organizational spread of high-intensity and low-intensity post-implementation “boosters”, and a “no booster” condition, and (iii) to compare the relative costs and impacts of each booster condition.

**Methods/design:**

SSaSSy is a two-phase mixed methods study. The overarching design is convergent, with qualitative and quantitative data collected over a similar timeframe in each of the two phases, analyzed independently, then merged for analysis and interpretation. Phase 1 is a pilot involving up to 7 units in 7 MB nursing homes in which SCOPE was piloted in 2016 to 2017, in preparation for phase 2. Phase 2 will comprise a quasi-experiment with two treatment groups of low- and high-intensity post-implementation “boosters”, and an untreated control group (no booster), using pretests and post-tests of the dependent variables relating to sustained care and management practices, and resident outcomes. Phase 2 will involve 31 trial sites in BC (17 units) and AB (14 units) nursing homes, where the SCOPE trial concluded in May 2019.

**Discussion:**

This project stands to advance understanding of the factors that influence the sustainment of practice changes introduced through evidence-informed practice change interventions, and their associated sustainability. Findings will inform our understanding of the nature of the relationship of fidelity and adaptation to sustainment and sustainability, and afford insights into factors that influence the intra-organizational spread of practice changes introduced through complex interventions.

Contributions to the literature
Post-implementation studies of intervention sustainability, like that described in this protocol, are rare.Once intervention implementation supports are removed, the effects of interventions are susceptible to natural decay and our understanding of how to sustain the use of the new knowledge conveyed in interventions, post-implementation and long-term, is poor.This protocol describes a study that will contribute to knowledge on the sustainment (sustained use), sustainability (sustained benefits), and spread of evidence-based practice innovations in health care.The study will be situated in the under-studied institutional long-term care sector.

## Background

Considerable investment is made to generate research knowledge intended to improve the quality and delivery of health care. Knowledge of this type, particularly when it is complex, is frequently conveyed via evidence-based practice interventions, and the costs expended to implement these interventions are similarly substantial [1]. Once intervention implementation “supports” are removed, the initial effects obtained through these interventions are susceptible to natural decay [2–4]. The long-term durable sustainment of evidence-based changes to practice is challenging [1, 5, 6].

While sustainability has been identified as “one of the most significant translational research problems of our time” (1: 2), post-implementation studies of practice change sustainability in health care are rare [7–11] and so it follows that our understanding of the factors that influence sustainability is generally poor. Failure to sustain evidence-based changes or innovations to practice means that the intended improvements to care are short-lived, that the practice innovations’ further scale-up and spread is unlikely, and that real losses are incurred on research investment, often made with public funds. *This protocol describes a study that aims to contribute to our understanding of the inter-related phenomena of sustainability, sustainment, and spread of evidence-informed, complex practice change interventions*.

### Unpacking the concept of sustainability

While the concept of sustainability is still maturing [3, 4, 12], work in this area has recently acknowledged a useful distinction between sustainability and sustainment [4, 8]. With a focus on lasting benefits, *sustainability* generally refers to the extent to which “an evidence-based intervention can deliver its intended benefits over an extended period of time after external support from the donor agency is terminated” ([13]: 118); whereas, *sustainment* refers to the continued enactment of processes, practices, or work routines that are conveyed and learned through an intervention [4, 8]. While the concept of spread is generally discussed separately [14], we suggest that there is likely a link between spread and the concepts of sustainability and sustainment, given that the spread of the practices and benefits introduced through an intervention, from one part of an organization to other parts or from one organization to another, is unlikely to take place without some degree of retention of these processes and benefits within the originating unit or organization. As with sustainability, the importance of understanding the processes and factors that influence the spread of healthcare innovations, including practice innovations, are highlighted in the implementation literature, albeit separate from the literature on sustainability [9, 15, 16].

### Approaches to studying sustainability: fidelity versus adaptation

To date, studies of sustainment and sustainability invoke one of two dominant and competing approaches: the fidelity approach, and the adaptation approach [3, 7]. The *fidelity approach* focuses on implementation fidelity and is the most common approach used to examine sustainability. Fidelity is defined as the extent to which an intervention program follows the originally intended implementation plan and faithfully delivers the research-informed components of the intervention [11, 17]. This approach contends that deviation from the intended intervention content and delivery protocols during implementation—that is, “program drift” and “low fidelity”—will inevitably lead to diminished benefits/outcomes both during and after implementation, once intervention support is withdrawn [8, 18].

By contrast, the *adaptive approach* ascribes importance to the co-evolution of the intervention and the organizational context into which it is introduced [7]. This approach suggests that overemphasis on fidelity and adherence, “relative to generalizability and adaptation”, increases the risk of creating interventions—including practice changes and the processes to effect them—that will not “fit” within complex or changeable settings ([8]: 2), and that while changes to the intervention may reduce fidelity they may lead to *improved* fit to local context and *enhanced* outcomes/benefits [8, 9, 18, 19].

In this study, fidelity versus adaptation is of interest to us to the extent that it is, or is not, related to post-implementation sustainment and sustainability of practice change. High implementation fidelity *during* an intervention may contribute to sustained use and benefits. Conversely, the adaptive perspective suggests that sustainability and sustainment is achieved in organizations that are adept at striking a balance between fidelity and responsiveness to the implementation context. The bottom line is that what is done during implementation, in addition to what is done afterwards, is thought to affect the sustainment, sustainability and spread of practice changes conveyed through an intervention—but we do not know precisely how. Work to further our understanding of relationships amongst fidelity, adaptation, sustainment, sustainability, and spread is needed and there is almost no literature on these dynamics. SSaSSy will contribute to this understanding.

### Study context

SSaSSy is a post-implementation study of sustainment (continued use), sustainability (lasting benefits), and spread (beyond the initial implementation setting) of the practice changes conveyed through an evidence-informed, Care Aide-led, facilitation-based quality-improvement intervention called SCOPE (*Safer Care for Older Persons (in long-term care) Environments*) that is the focus of a clinical trial being conducted in in Canadian nursing homes operating in the Provinces of Manitoba (MB), Alberta (AB) and British Columbia (BC) [NCT03426072]. In SCOPE, HCA-led teams lead quality-improvement initiatives focussing on one of three resident care areas identified as priorities by experts in long-term care, i.e., mobility, pain, and behavior [20]. The SCOPE intervention was piloted in nursing homes in AB and BC over 2010-2011. The impacts of the SCOPE intervention are described in several published articles:
In Norton et al. [21], the SCOPE pilot was shown to meet its primary objective of demonstrating the feasibility and utility of implementing the intervention in nursing homes relying upon the leadership of HCAs, and engagement of professional staff and leadership in facilitative roles. Specifically, of the 10 HCA-led QI teams in nursing homes that participated in the SCOPE pilot, 7 succeeded in learning and applying the improvement model and methods for local measurement, with 5 of the 10 teams showing measurable improvement in the chosen clinical areas.These impacts were corroborated in a follow-up study that examined the sustainability of elements of the SCOPE pilot [22]. In this article, sustained differences between participating/intervention units, and non-participating units, were observed in outcomes relating to quality-improvement activities (i.e., continuation of work according to the improvement model and principles learned in SCOPE), HCA empowerment, and satisfaction with quality of work life.As part of the SCOPE clinical trial, SCOPE was implemented in 7 units in MB nursing homes over 2017, somewhat earlier than the intervention was implementation in participating BC and AB units/homes. While the data for the MB homes will be analyzed in conjunction with that collected for homes in BC and AB, a recent retrospective qualitative analysis of the implementation experiences [23] of administrative leaders (sponsors), professional staff, and QI team participants in MB homes demonstrates effects akin to those observed in the SCOPE pilot. In addition to accruing observable benefits to residents who were the subjects of the QI initiatives formulated by the HCA-led QI teams in participating units in each MB home, SCOPE was observed to change the expectations and behaviors on the part of administrative leaders, professional staff, and—importantly—HCAs relating to their abilities to conduct small-scale, unit-level, evidence-informed quality-improvement initiatives [23].

Both SCOPE and SSaSSy are situated within a larger program of research, Translating Research in Elder Care (TREC) [24]. TREC was initiated in 2007 and focuses on the influence of organizational context on resident quality of care and safety in 94 nursing homes in the three Western Canadian Provinces [24]. Both SCOPE and SSaSSy rely on TREC’s longitudinal database that includes data on staff behavior, attitudes and quality of worklife; leader behavior; work environment (context); and care unit and nursing home characteristics (e.g., unit size, facility owner-operator model). Data are collected routinely from all levels of nursing home staff, and quality of care measures are collected on a quarterly basis across the 94 homes at the unit level [25] via the Resident Assessment Instrument—Minimum Data Set, version 2.0 (RAI-MDS 2.0).

### Study purpose and aims

SSaSSy focusses on a 1-year interval, 1 year *after* SCOPE implementation concludes. Phase 1 of SSaSSy is a pilot that will occur in 7 units in MB nursing homes where SCOPE was piloted over 2016–2017. The results of this pilot will inform the content of post-implementation “boosters”, designed to sustain or renew the application of the QI techniques and tools—the changes to care practice—conveyed through SCOPE. The relative effectiveness of the boosters compared to a no booster control will be tested in phase 2 in 31 more units in nursing homes in BC and AB, where SCOPE concluded in May 2019.

As a post-implementation study, SSaSSy presents a rare opportunity to systematically contribute to knowledge [22] on the sustainment and sustainability of complex practice changes conveyed through evidence-based interventions, and to examine spread—first, in the SCOPE pilot sites in MB and subsequently in the trial sites in BC and AB.

Specific aims of SSaSSy are:
To determine whether fidelity, site- or facility-initiated adaptation of aspects of the intervention, aspects of the implementing unit, and/or other aspects of nursing homes’ operations or structures, are associated with sustainment, sustainability and spread one year following implementation of practice changes conveyed through SCOPE.To explore the relative effects on sustainment, sustainability and intra-organizational spread of high- and low-intensity post-implementation “boosters” compared to “no booster”/natural decay; specifically, the extent to which there are:
sustained or renewed improvements in resident outcomes in clinical areas of focus targeted by the SCOPE intervention (deteriorating mobility, pain, responsive behavior) (*sustainability*),sustained or renewed changes in staff behaviors (reported use of best practices, use of SCOPE components and processes) (*sustainment*),sustained or renewed changes to staff work attitudes (work engagement, psychological empowerment, burnout, job satisfaction) and outcomes (organizational citizenship behaviors) related to work performance (*sustainability*),sustained or renewed changes to senior leadership support behaviors relating to staff engagement in SCOPE (*sustainment*),indications of *spread* to other units within the SCOPE intervention sites, and its extent.To compare the costs and effectiveness of each post-implementation support condition.

## Approach/methods

SSaSSy is a two-phase mixed methods study. The overarching design is convergent, with qualitative and quantitative data collected over a similar timeframe in each of the two phases, analyzed independently, then merged, interpreted and reported by means of joint display [26].

### Participating nursing home sites

SSaSSy will first take place in the nursing home units in MB that participated in the SCOPE pilot, and then in those in AB and BC that participated in the full SCOPE trial. These homes meet the inclusion criteria applied to the original SCOPE pilot, and trial: (i) the facility provides 24-h on-site housing and health care services care for older adults by professional (nursing) staff and others; (ii) the facility is registered with the provincial government; (iii) 90% of residents are aged 65 or over; (iv) RAI-MDS 2.0 has implemented since January 2011; (v) facility operations are conducted in the English language; (vi) urban facilities are located within designated health regions and within 110 km of the TREC-designated hub for the health region.

### Phase 1

The first study phase, in MB, entails developing the content of the two post-implementation support conditions—low- and high-intensity “boosters”—through consultation with participants in the SCOPE pilot sites in MB nursing homes; piloting data collection instruments with SCOPE pilot site participants that explore factors relating to sustainability, sustainment and spread including fidelity and adaptation relevant to aim 1; piloting the low- and high-intensity “boosters” in up to 7 SCOPE pilot sites in MB while collecting quantitative and qualitative data relevant to aim 2 (sustainability, sustainment, spread); and piloting a data collection instrument intended to capture the costs related to each of the post-implementation support conditions.

#### SSaSSy booster content

The preliminary content of the low- and high-intensity boosters is informed by three prior studies relating to the SCOPE intervention [22, 23, 27] that highlight four components of the SCOPE pilot that appear to be highly relevant to its implementation: (i) the presence of team and senior sponsors who learn leadership skills intended for use in supporting the Care Aide-led unit QI Teams by securing resources; (ii) face-to-face “Learning Congresses” in which Teams build QI-related skills and where exchanges with care teams from other facilities enhance learning and team efficacy; (iii) quality advisors who fill both supportive and educational roles relating to applying QI techniques on the part of the QI Teams, and change management leadership coaching of sponsors; and (iv) the use of “setting aims” as an effective mechanism for changing QI Team members’ behavior. The mix of these booster components, and their intensities, will be further informed through a focus group consultation of 2–3 decision-makers familiar with the MB SCOPE pilot, 2–3 QI experts, and 2 researchers with expertise in implementation science.

#### SSaSSy booster pilot

The low- and high-intensity boosters will be piloted in up to 7 units in 7 MB homes (potentially 3 low-intensity booster units, 4 high-intensity booster units) for 7 months, starting June 2019. The pilot interval will be followed by data analysis and refinement of boosters where we will focus on: (i) assessing relationships between the boosters’ contents and sustainment, sustainability, and spread; (ii) the clarity of the booster content from the perspective of the QI Teams; and (iii) the adequacy of the modes of delivery. Quantitative and qualitative data will be collected during the pilot; see Table 1 for a summary of measures relevant to each study aim.

**Table 1 Tab1:** SSaSSy aims, measures and analyses

Aim		Data/measures	Analysis
Aim 1. Explore site adaptation and/or contextualization		Semi-structured in-person interviews with the QI Team lead, senior sponsor, and QI advisor	A hybrid approach of qualitative methods will be used, thematic analysis [28], which incorporates both an inductive approach that allows themes to emerge from the data [29] and a deductive a priori template-of-codes approach [30] based on research we review above. Audiotapes of the interviews will be transcribed verbatim and data analysis will be completed using line-by-line coding and constant comparative methods [31]
Aim 2: Explore the relative effects of the high- and low-intensity boosters	2a: Sustainability: Sustained or renewed improvements to quality of resident care	Unit-level quality indicators generated using RAI-MDS 2.0 data on resident outcomes (mobility, pain, behavior)	Run charts will be generated for the RAI-MDS data^(i)^ collected SSaSSy start for each of the three quality indicators for each unit (RAI data elements MOB01/MOB1A; PAI0X/PAN01; BEHD4/BEHI4). For the clinical area on which QI Teams focus, we will analyze the relevant RAI-MDS quality indicator using statistical process control methods [32] and a procedure that members of our research team developed for the SCOPE proof of principle study [21] which categorizes control charts in terms of demonstrated changes to performance.
Notes:			
(i) RAI-MDS 2.0 is a valid, reliable standardized assessment of resident outcomes that includes a comprehensive set of clinical outcomes and captures characteristics of nursing home residents and their care [33]. Each resident has a full assessment (~450 items) performed on admission, and a shorter (300 item) assessment is performed quarterly. These data are routinely collected from all 94 participating TREC sites, from which SCOPE study sites were drawn, and are the source of SSaSSy’s resident outcome data			
	2b & 2d: Sustainment: Sustained or renewed changes in staff behavior and senior leadership support behaviors	SCOPE templates completed by QI Team leads. diaries and feedback reports completed by QI Advisors	SCOPE Templates^(ii)^ will be analyzed, using document analysis [34, 35], at two junctures: analysis of the SCOPE Templates accrued over SCOPE implementation, and over the SSaSSy booster interval to determine peri-intervention fidelity and post-intervention fidelity, respectively. First, gross-grained assessments of the use/non-use of the templates (sustainment) by each QI Team will be made (i.e., were templates complete and posted on intranet site available to Teams). Thematic analysis (see above) will then be used to analyze the contents of the QI Team templates, as well as the QI advisor diaries and feedback reports^(iii)^
	2c: Sustainability: Sustained or renewed changes to staff work attitudes and outcomes related to work performance	TREC HCA Survey [36]	While quantitative data will be collected and analyzed over the course of the project, SSaSSy likely will not be adequately powered for statistical inference. Descriptive statistics including statistics of central tendency, dispersion, and standard deviation will be computed for each unit-level variable, for each booster arm collected through the TREC Survey waves. However, if changes in the primary outcome of the SCOPE intervention, Care Aide-reported *conceptual use of best practices*, are sufficient over the booster interval (e.g., an effect size of 0.29), we will use one-way ANOVA (repeated measures, within-between interaction) to test for “pre–post” differences in the means of each variable within and between groups/booster arms, followed by Tukey–Kramer test for significant differences between all pairs of groups if appropriate (where distributions are not normal the Kruskal–Wallis test will be used, and where data are heteroscedastic Welch's ANOVA will be used). In the more likely event that changes of this magnitude do not occur, we will compute p-values by time point before and after the SSaSSy booster interval. We are constrained in our sample size because we are studying the post-implementation of a trial with a fixed number of experimental sites.
(ii) SCOPE Templates refer to documents introduced during SCOPE implementation, in the all-team Learning Congresses, that are designed to assist care aide-led QI Teams in planning and managing their QI projects, and measuring and reporting their progress against their project aims			
(iii) The quality advisors keep diaries in which they prepared structured summaries of each interaction with the QI Teams, whether face-to-face or telephone, outside of the all-team Learning Congresses. Quality advisors also prepare written, structured, quarterly feedback reports for each QI Team			
	2e: Spread: Indications of spread to other units within the SCOPE intervention sites	Semi-structured in-person interview with the QI Team lead, senior sponsor, and QI advisor	As above
Aim 3: Compare the effectiveness and costs of post-implementation support arms		Documentation of resources and associated costs for low- and high-booster conditions	This cost analysis is exploratory in nature. We plan a simple, disaggregated reporting of costs. We will report the intervention costs (costs to deliver the boosters) separately from the costs incurred by the participating units. Each unit will report their incurred costs for staff, training and materials and supplies. Disaggregated presentation will allow units to understand what is driving the costs and identify possible areas where costs could be modified within the overall intervention

### Phase 2

The second study phase will use a quasi-experimental design [37] to evaluate the relative effectiveness of the three post-implementation support conditions: two treatment groups (low-, and high-intensity post-implementation boosters) and an untreated control group (no booster). Pretest and post-test data [37] relating to sustainment and sustainability will be collected through TREC surveys and via unit-level RAI-MDS 2.0 quality indicators. Phase 2 will begin in June 2020 and involve trial sites in BC (17 units) and AB (14 units), where SCOPE implementation concluded in May 2019. Specifically, the untreated control group (10 units) will receive no post-implementation support, one treatment group (10 units) will be provided with a low-intensity booster, and the second treatment group (11 units) will receive a high-intensity booster.

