### Integration

In this mixed methods study, quantitative and qualitative findings will be integrated at the interpretation and reporting stage [26, 38]. Independent analyses of the qualitative and quantitative data will serve to organize the data in a format based on thematic relevance (sustainability, sustainment, spread, influencing factors) that permit merging and subsequent higher order integration. This will be accomplished in two ways: first, the quantitative and qualitative data will be integrated using a joint display. Second, a narrative approach will be used to describe the quantitative and qualitative results thematically. The narrative will offer intra-group and inter-group comparisons within and between booster arms. Figure 1 offers a flow diagram for phase 2.

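### Aim 2a asks for booster effects relative to no booster, but the only quantitative analysis specified for it judges each unit against its own past and gives no arm-level contrast

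*Protocol article*

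**What the plan says.** **The question.** Aim 2 (Study purpose and aims) is "To explore the relative effects on sustainment, sustainability and intra-organizational spread of high- and low-intensity post-implementation" boosters, set against no booster or natural decay. Item 2a is sustained or renewed improvement in mobility, pain and responsive behaviour. The Phase 2 section says the design will "evaluate the relative effectiveness of the three post-implementation support conditions" and names the unit-level RAI-MDS indicators among the pretest and post-test data. On the arms, "the untreated control group (10 units) will receive no post-implementation support", "one treatment group (10 units) will be provided with a low-intensity booster", and a third group of 11 units receives the high-intensity booster.

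**The analysis for 2a.** In Table 1, row 2a, run charts are drawn "for each of the three quality indicators for each unit". For the team's focus area, "we will analyze the relevant RAI-MDS quality indicator using statistical process control methods", together with a procedure from an earlier study "which categorizes control charts in terms of demonstrated changes to performance". The row ends there.

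**Other relevant text.**
- Row 2c (staff survey) does give statistics for each booster arm and a conditional between-arm ANOVA.
- The section on non-equivalent dependent variables uses the two non-target indicators against shared threats to validity.
- Integration says: "The narrative will offer intra-group and inter-group comparisons within and between booster arms".
- Strengths and limitations says the study is not powered for inference and will examine relative effectiveness with descriptive statistics.

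**The concern.** A control chart asks whether one unit's process has departed from its own earlier level. Aim 2a asks whether units with a booster changed by a different amount from units without one. Row 2a answers the first question and does not carry the result to the second. Row 2c shows that the same table states arm-level analyses where they are intended.

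Two things are at stake. With 10 or 11 units per arm, reducing a quarterly series to a category discards information the study can ill afford to lose. And part of the question is whether a booster holds gains against natural decay. A unit that merely stays level has no reason to show an improvement signal, so a booster that works by preventing decline could look as if it did nothing.

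**Working it through.** The article gives no power, error rate or effect size for 2a, so there is no figure to reproduce. The arm sizes are consistent: 10 + 10 + 11 = 31 = 17 + 14.

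**Inputs from the article.** 10 control units, 11 high-intensity units, quarterly assessments, and a 1-year interval, hence about 4 booster-period points per unit.

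**Assumed inputs (not in the article).** 8 pre-booster quarters; within-unit quarterly SD of 1; between-unit SD of true change (s) of 0.3, with 1.0 as the unfavourable case; independent quarters. Charts are XmR, signalling improvement on one point beyond 3 sigma or two of three beyond 2 sigma. The plan names no test on chart categories, so Fisher's exact test stands in for a formal reading of them.

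**1. Contrast of unit-level change, high v none, true effect 1 SD.**
- Variance of a unit's change = s² + 1/8 + 1/4.
- s = 0.3: 0.09 + 0.375 = 0.465, SD 0.682. SE = 0.682 × √(1/10 + 1/11) = 0.298. Non-centrality 1/0.298 = 3.36 on 19 df, power about 89%. Simulation gave 88% to 89%.
- s = 1.0: 1 + 0.375 = 1.375, SD 1.173, SE 0.512, non-centrality 1.95, power about 46%. Simulation gave 45% to 47%.

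**2. Chart categories, same effect, s = 0.3.** About 7% of control units and 30% of high-intensity units signal improvement.
- With no control signals, Fisher's test needs at least 5 of 11 booster units: p = (462 + 252)/20,349 = 0.035. Four of 11 gives p = 0.09.
- The expected number is 0.30 × 11 = 3.3.
- P(no control signal) = 0.93^10 = 0.484; P(5 or more of 11 at 30%) = 0.210; product 0.10. The remaining rejection outcomes bring power to about 11%, as simulated.

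**3. Shared drift, no booster effect.** Simulated signal rates, control v booster, are about 30% v 31% at a 1-SD drift and 47% v 48% at 1.5 SD. Fisher's test rejects falsely in 2% to 3% of trials. Drift raises signals equally in both arms.

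**4. Booster that only prevents a 1-SD decline.** Booster units have zero true change, so improvement signals stay at the false-alarm rate of about 7%. The arm difference in change is still 1 SD, so the power in step 1 still applies.

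**5. Second model.** Quarterly p-charts, baseline rate 20%, 25 or 40 residents per unit, 8 + 4 quarters, and an added rule that four points beyond 1 sigma signal. Power, high v none:

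| True effect | SD of change | Chart categories | Contrast of change |
|---|---|---|---|
| 5 points | 3 points | 0–3% | 49–66% |
| 10 points | 3 points | 31–76% | about 98% or more |
| 10 points | 6 points | 31–49% | 82–85% |
| 10 points | 9 points | 21–28% | 54–60% |

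A shared 10-point improvement again gives equal signal rates in all three arms (about 36–37% with 25 residents, 55–56% with 40). If the high-intensity booster fully offsets a 10-point decline, 2–3% of its charts signal improvement, while the contrast has 95–98% power (SD 3 points).

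**The case against.** The strongest reply has four parts.

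**Shared drift.** A reader might infer that a policy or coding change affecting every unit would be taken for booster benefit. The documents do not support this. Control units are charted too, an inter-group narrative is planned, and the non-target indicators are included expressly against shared threats. Step 3 shows no bias when the arms are read together. What remains is narrower: the article does not say that control and booster charts will be read together, process control is applied only to the focus-area indicator, no rule says how the non-target indicators enter the arm comparison, and drift peculiar to the target indicator would escape them.

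**A comparison is planned.** It would be wrong to say there is none. The narrative and the descriptive statistics are between-arm steps, but neither defines an arm-level quantity for 2a.

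**The power figures rest on assumptions.** This stands. Chart rules, baseline length, unit size and SDs are all assumed, and no Fisher test is planned. The categorisation procedure is in a source not at hand; it may have more than two categories and may flag deterioration in control units. Serial correlation between quarters was ignored and would change every rate.

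**The aim is exploratory and the article is condensed.** Both are true. But the article chose and stated a method for 2a that does not match the aim, which differs from leaving detail to a fuller document. Low power argues for the more efficient summary.

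**Conclusion.** The point holds as a mismatch between question and analysis, with a material loss of efficiency. Row 2a specifies a within-unit method for a between-arm aim. At a 1-SD effect, chart categories give about 11% power (SD of change 0.3). The contrast of unit-level change gives about 89% at that SD and still about 45% if the SD is 1.0. The contrast was the better of the two in every setting with a true effect tabulated above, under both models; that ordering is the robust result, not the particular percentages.

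A reader might go further and say a real effect would mostly be missed. That fits moderate effects but not large ones: in the first model chart-category power passes 40% at 1.5 SD and is about three quarters at 2 SD, and in the second it reaches 76% in the most favourable 10-point setting. The weakness for a booster that only prevents decay follows from what an improvement signal is, though deterioration signals in control units could recover part of it if the procedure records them.

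**What to change.** Keep the run charts and control charts as unit-level description. Add to Table 1, row 2a, an exploratory between-arm contrast of the quarterly unit-level target indicator. This can be a regression of each unit's booster-period mean on arm and its pre-booster mean, or a mixed model with a unit random effect, quarter, and arm by period. Standardise by indicator and adjust for focus area. Report high v none and low v none with 95% intervals.

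Run the same contrast on the two non-target indicators as the stated check for shared threats. State that no relative booster effect will be claimed from the chart categories of booster units alone.

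The cost is wording and modest modelling, since the indicators are already collected quarterly in all arms. There are two downsides. Three different indicators must be put on a common scale. And the intervals will be wide: under the assumptions above, the half-width for high v none is 2.093 × 0.298 = 0.62 SD, or 2.093 × 0.512 = 1.07 SD in the unfavourable case. The estimates should be labelled exploratory, in line with the article's own statement on power.
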